## Abstract

**Background:**

Neurobehavioral disabilities occur in 5–15 % of preterm infants with an estimated 50–70 % of very low birth weight preterm infants experiencing later dysfunction, including cognitive, behavioral, and social delays that often persist into adulthood. Factors implicated in poor neurobehavioral and developmental outcomes are hospitalization in the neonatal intensive care unit (NICU) and inconsistent caregiving patterns. Although much underlying brain damage occurs in utero or shortly after birth, neuroprotective strategies can stop lesions from progressing, particularly when these strategies are used during the most sensitive periods of neural plasticity occurring months before term age. The purpose of this randomized trial is to test the effect of a patterned feeding experience on preterm infants’ neurobehavioral organization and development, cognitive function, and clinical outcomes.

**Methods:**

This trial uses an experimental, longitudinal, 2-group design with 120 preterm infants. Infants are enrolled within the first week of life and randomized to an experimental group receiving a patterned feeding experience from the first gavage feeding through discharge or to a control group receiving usual feeding care experience. The intervention involves a continuity of tactile experiences associated with feeding to train and build neuronal networks supportive of normal infant feeding experience. Primary outcomes are neurobehavioral organization as measured by Neurobehavioral Assessment of the Preterm Infant at 3 time points: the transition to oral feedings, NICU discharge, and 2 months corrected age. Secondary aims are cognitive function measured using the Bayley Scales of Infant and Toddler Development, Third Edition at 6 months corrected age, neurobehavioral development (sucking organization, feeding performance, and heart rate variability), and clinical outcomes (length of NICU stay and time to full oral feeding). The potential effects of demographic and biobehavioral factors (perinatal events and conditions of maternal or fetal/newborn origin and immunologic and genetic biomarkers) on the outcome variables will also be considered.

**Discussion:**

Theoretically, the intervention provided at a critical time in neurologic system development and associated with a recurring event (feeding) should enhance neural connections that may be important for later development, particularly language and other cognitive and neurobehavioral organization skills.

**Trial registration:**

NCT01577615 11 April 2012.

**Electronic supplementary material:**

The online version of this article (doi:10.1186/s13063-015-0781-3) contains supplementary material, which is available to authorized users.

## Background

Despite a survival rate that exceeds 85 %, between 5–15 % of very preterm infants born at less than 28 weeks post-menstrual age (PMA) will have long-term neurodevelopmental consequences of prematurity including cerebral palsy and severe neurosensory impairment [1]. Moreover, an estimated 50–70 % of very low birth weight preterm infants (≤1500 g) have late onset neurodevelopmental dysfunction, including cognitive, behavioral, and social delays [2]. These dysfunctions often persist into adulthood [3], making preterm birth one of the most costly and devastating of all health events [4].

A major reason for increased risk of poor neurodevelopmental outcomes is the structural differentiation of the central nervous system (CNS) that occurs rapidly between 23 and 32 weeks of gestation [5]. In a term pregnancy, this differentiation occurs in utero, with a “system” that is designed by nature to support the biologic processes that are occurring. However, the neurologic system of infants who are born preterm develops within the more noxious environment of the neonatal intensive care unit (NICU), which is often characterized by high sound and light levels and by inconsistent caregiving patterns [6–10]. Moreover, even when efforts are made to improve NICU caregiving using developmental care models, the prevalence of poor neurodevelopmental outcomes is high and the incidence appears to be increasing, perhaps due to the complex relationships among biologic and environmental risks, caregiving behaviors, and the timing, size, and site of brain insults.

Few interventions have been shown to reduce neurobehavioral disorganization and poor neurodevelopment in children who were born preterm. Improvement in neurodevelopmental outcomes depends on interventions that take advantage of the preterm infant’s capabilities [11]. Further, it is important that relationships among multiple risk factors, interventions, and outcomes are articulated so that interventions can be tailored specifically to infants with varying risk profiles [12].

Our intervention, a patterned feeding experience (PFE), is not currently used in most neonatal settings. The intervention is based on principles of neural plasticity and neuroprotection and is designed to take advantage of neuronal synaptic development and both experience-expectant and experience-dependent characteristics of the developing brain [13]. In addition, the intervention takes advantage of a regularly occurring caregiving and life-sustaining event in the life of an infant–feeding. The PFE intervention involves a continuity of tactile experiences associated with feeding to train and build neuronal networks supportive of the normal experience. There are virtually no accepted and no tested caregiver behaviors related to enteral feedings in preterm infants, although some recent research has produced evidence for a positive effect of greater caregiver sensitivity to the infant during feeding [14]. Theoretically, our intervention provided at a critical time in neurologic system development and associated with a recurring event such as feeding should enhance neural connections that may be important for later development, particularly language and other cognitive and neurobehavioral organization skills [15].

The overall objective of this study is to test the effect of a PFE from birth to NICU discharge for infants born at 32 weeks gestation and younger. The primary aim of the study is to test the effect of a PFE on neurobehavioral organization at 3 time points: the transition to oral feedings, NICU discharge, and 2 months corrected age (48 weeks PMA). Secondary aims are to test the effect of a PFE on 1) cognitive function at 6 months corrected age; 2) neurobehavioral development; and 3) clinical outcomes including time to first oral feeding, time to full oral feeding, and time to discharge. An exploratory aim is to describe the potential effects of perinatal and infant risk factors including immunologic and genetics influences on the outcome variables (neurobehavioral organization, cognitive function, neurobehavioral development, and clinical outcomes). We hypothesize that infants who receive the PFE will have improved neurobehavioral organization, cognitive function, neurobehavioral development, and clinical outcomes compared to infants who receive usual feeding care in the NICU.

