### Intervention

The study intervention has two phases using a tactile experience designed to pattern the neurologic system’s theoretical expectation for feeding experience. Phase 1, a period of “attended gavage,” begins within 24 hours of the first gavage feeding, which is generally provided before 72 hours of life. Attended gavage includes tactile containment during the entire gavage infusion by gravity plus 5 minutes. For infants too ill to be removed from the incubator, tactile containment consists of gentle hand containment (placing one hand lightly over the shoulder area and one hand lightly over the lower extremities). If medically stable, the infant is swaddled and removed from the incubator and held. Infants are also offered nonnutritive sucking (NNS) as part of every attended gavage feeding based on prior research showing that NNS facilitates behavioral organization. Instructions related to the tactile containment, swaddling/holding during gavage, and use of NNS are provided for all nursing staff and parents of infants in the intervention group. Gavage feedings are most often provided on a schedule of every 3 hours. Infants on continuous feedings, which may be needed for some infants primarily because of gastric reflux, receive the attended protocol every 3 hours for 15 minutes. Phase 1 of the intervention has varying duration, lasting as long as 12 weeks for infants born at 23 weeks PMA. Attended gavage is a change in practice for most NICUs so we use a team of well-trained study nurses who provide the attended gavage feedings for a minimum of 50 % of the feedings daily. Nursing staff or parents may provide additional attended gavage feedings. We record the occurrence of each attended feeding including who provided the intervention (parent, nursing staff member, or study nurse) and include that “dose” as a covariate in our analyses.

Phase 2 begins when infants in the intervention group begin oral feedings. When an oral feeding is attempted, the infant is held outside the incubator in a swaddled, flexed position either upright or side-lying. We record the volume of feeding prescribed and the amount consumed at each feeding. Infants who are unable to complete the prescribed volume orally or unable to orally feed receive attended gavage as described in Phase 1.

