#### Clinical outcomes

Time to full oral feedings, the duration (in days) between the initiation of oral feeding and the achievement of full oral feeding, and length of stay, the number of days between the start of oral feeding and discharge to home, are also measured. Full oral feedings are achieved when the infant is consuming all nutrients orally by breast or bottle without intravenous supplementation or gavage feeding for 24 hours.

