The secondary aims require similar comparisons between study groups on secondary outcomes (cognitive functioning, neurobehavioral development, and clinical outcomes). To test secondary aim 1, differences between the 2 groups on the cognitive outcome measure (BSIDIII cognitive subtest scaled score) at 6 months corrected age will be tested using an ANCOVA with morbidity (NMI) and birth gestation used as covariates. To test secondary aim 2, 4 analyses will be performed, one for each of the feeding-related neurobehavioral outcomes (sucking organization, 2 measures of feeding performance, and HRV). The modeling will be done as above with a repeated-measures mixed-model approach with covariates (birth gestation, morbidity). To test secondary aim 3, separate ANCOVA analyses of the clinical outcomes (time to full oral feeding and length of stay) will be used to compare the 2 groups with the birth gestation age and morbidity covariates.

The intent of the exploratory aim is to identify risk factors of poor neurobehavioral development and cognitive dysfunction in preterm infants. We will test the assumed comparability of randomly assigned groups prior to undertaking further analyses. Secondary analyses will focus on the interactions between risk factors and the intervention differences by first screening the risk factors for effects at *P* = 0.2 and then developing a single exploratory model that includes all of the risk factors that significantly influence the outcome differences between the groups. Additional analyses will focus on the findings for neurobehavioral development including sucking organization and feeding performance, HRV, and clinical outcomes, first by examining the relationships between the risk factors and the components of neurobehavioral development and then by assessing the relationships among the components of neurobehavioral development and the primary outcome measure, the NAPI score (neurobehavioral outcome). The final goal is to identify a model of risk factors, modifiers (measures of neurobehavioral development), and mediators (intervention) that have an effect on the differences between groups.

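### Secondary aim 3 names time to first oral feeding, but the article neither defines nor analyses it, and both clinical outcomes it keeps are counted from that event

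*Protocol article*

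**What the plan says.** The article describes the clinical outcomes in four places.

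- Background, aims: the third secondary aim is to test PFE on "clinical outcomes including time to first oral feeding, time to full oral feeding, and time to discharge".
- Abstract, Methods: "clinical outcomes (length of NICU stay and time to full oral feeding", with nothing on the first oral feeding.
- Measures, Clinical outcomes: time to full oral feeding is "the duration (in days) between the initiation of oral feeding and the achievement of full oral feeding". The other outcome is "length of stay, the number of days between the start of oral feeding and discharge to home".
- Data management and analysis, secondary aim 3: "separate ANCOVA analyses of the clinical outcomes (time to full oral feeding and length of stay) will be used", adjusted for birth gestation and morbidity.

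Two further sections bear on the point. Under Intervention, Phase 1 "begins within 24 hours of the first gavage feeding, which is generally provided before 72 hours of life", and Phase 2 starts with oral feeding. Under Sample, infants who for medical reasons cannot move to oral feeding by 40 weeks PMA leave the study.

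**The concern.** A named objective drops out between the aims and the analysis. This is not detail left to a fuller plan. The article itself lists which aim 3 outcomes receive an ANCOVA, and with which covariates, and that list conflicts with its own aim.

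Two things are at stake. First, the hypothesis of improved clinical outcomes would be judged on two of its three stated parts, and either list could be cited once results are known. Second, the missing outcome is the time origin of the two that remain. Parents, NICU staff and study nurses know the assignment (Randomization to groups), and the start of oral feeding follows randomization. If that start differs between groups, the two analysed durations shift with it, and no planned comparison would show why.

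**Working it through.** **1. The lists side by side**

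| Place | First oral feeding | Full oral feeding | Discharge |
|---|---|---|---|
| Background, aims | named | named | time to discharge |
| Abstract, Methods | absent | named | length of NICU stay |
| Measures, Clinical outcomes | not defined | days from start of oral feeding | length of stay, days from start of oral feeding |
| Analysis, secondary aim 3 | no analysis | ANCOVA | ANCOVA of length of stay |

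Three outcomes are named in the aim, two defined and two analysed, so 3 − 2 = 1 has neither a definition nor a test. The last column also changes meaning: the first two rows, read in the ordinary way, describe a stay that includes the gavage period, and the third does not.

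**2. The plan's own figure**

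Power analysis gives no figure for secondary aim 3 and refers to aim 1: a difference of 2 units, SD 3, 89% power. With 120 × (1 − 0.20) = 96 infants, 48 per group, a standardized effect of 2/3 = 0.667 and two-sided 0.05, the t-test has 89.8% power (normal approximation 90.4%). The figure is reproduced. It is not in dispute and does not settle which outcome list is meant.

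**3. What the shared origin does**

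Let B be birth, F first oral feeding, U full oral feeding and D discharge, all in days.

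- Time to first oral feeding = F − B (not in the plan)
- Time to full oral feeding = U − F = (U − B) − (F − B)
- Length of stay as defined = D − F = (D − B) − (F − B)

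Write Δ for the PFE mean minus the usual-care mean:

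- Δ(U − F) = Δ(U − B) − Δ(F − B)
- Δ(D − F) = Δ(D − B) − Δ(F − B)

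The article gives no expected value for Δ(F − B). As an illustration only, assume that age at full feeding and age at discharge are the same in both groups:

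| Assumed Δ(F − B) | Δ time to full feeding | Δ length of stay |
|---|---|---|
| −3 days (PFE earlier) | 0 − (−3) = +3 | 0 − (−3) = +3 |
| 0 days | 0 | 0 |
| +3 days (PFE later) | 0 − 3 = −3 | 0 − 3 = −3 |

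An earlier start makes both outcomes look worse, and a later start makes both look better, although no infant reaches full feeding or home sooner or later. The shift is one for one at any size. The identity is exact on the day scale for the same infants and covariates. It becomes approximate if the outcomes are transformed, which the analysis section allows.

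**4. Choice of scale**

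PMA at first oral feeding is gestation at birth plus F − B. With birth gestation as a linear covariate, both scales give the same adjusted group difference. Without that adjustment they differ by the between-group difference in gestation at birth.

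**The case against.** The case against making much of this has several parts.

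- The date of first oral feeding has to be recorded in both groups, because it is time zero for both retained outcomes. This stands: what is missing is a definition and a comparison, not data. A reader might infer that the question cannot be answered by this trial, and the documents do not support that.
- The wording in Measures, that the two durations are measured as well, need not be exhaustive. This softens that section. It does not help the analysis section, whose list is closed.
- A reader might infer that first oral feeding is the one clinical outcome on which Phase 1 acts directly. The article does not say so. Under Intervention, attended gavage continues in Phase 2 for feeds not completed by mouth, so it also runs through the period that time to full oral feeding measures.
- A reader might infer that a harmful delay would stay hidden. That goes too far. Removals at 40 weeks PMA should appear by group under CONSORT reporting, and an independent board meets twice a year. A delay short of that threshold is still covered by no planned comparison.
- That no analysed outcome covers the time before oral feeding depends on the Measures definition of length of stay. The ordinary sense of the abstract and the aim would include it. This stands as a condition, and it shows a second conflict to be settled.
- Deleting the item from the aim would also remove the contradiction. That is true, but it would leave the shared-origin problem in place.

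**Conclusion.** The point holds as an internal contradiction: one of three named clinical outcomes in secondary aim 3 has no definition and no analysis. It should be corrected, and it is limited in reach, since the primary NAPI analysis, the sample size and data collection are unaffected.

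It is more than editorial because, under the definitions in Measures, both retained outcomes begin at a post-randomization event in a trial where carers know the assignment. Their group differences cannot be read safely without the comparison at that event. This does not show that they are biased: whether PFE shifts the first oral feeding is unknown, and the 3-day figures are an assumption used to show direction.

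A reader might also extend the 12-week maximum length of Phase 1 to a typical length for more mature infants. The article gives that maximum only for infants born at 23 weeks and states no typical PMA at first oral feeding, so the uncovered interval cannot be sized for the sample as a whole.

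**What to change.** 1. In Measures, Clinical outcomes, define time to first oral feeding as days from birth to the first oral feeding. If PMA at first oral feeding is reported instead, keep birth gestation as a linear covariate so that the adjusted difference is the same.
2. In Data management and analysis, add it as a third aim 3 ANCOVA with birth gestation and morbidity as covariates.
3. State how infants removed for not making the transition by 40 weeks PMA are counted in this comparison. They have no observed value, and leaving them out without comment would restrict it to infants who made the transition.
4. Make the outcome lists in the abstract and the aims match, and reconcile time to discharge and length of NICU stay with the Measures definition, which starts at oral feeding.

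If the outcome is not intended, remove it from the aim with a reason. In that case the two remaining durations still need a statement of how a group difference in their common starting point will be handled.

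The cost is one more secondary analysis and a counting rule. No new data are needed.

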## Methods

### Design

The study is a longitudinal randomized control trial with two groups of preterm infants, one receiving PFE from the first gavage feeding through full oral feedings to discharge and one receiving usual feeding experience. Ethical approval for all aspects of the study was obtained from the Institutional Review Board, Cincinnati Children’s Hospital Medical Center (2011–0871). A data and safety monitoring plan is in place and a data and an independent safety monitoring board meets biannually to review trial conduct including assessment of any adverse events. All study data are kept confidential and in stored in secure data bases. The protocol is guided by the Standard Protocol Items: Recommendations for Interventional Trials (SPIRIT) [16], 2013 statement, which can be found in Additional file 1, and the Consolidated Standards of Research Trials (CONSORT) [17].

### Setting

The study is being conducted in two NICUs that are staffed by the same physician group, thus providing similarity in medical care related to feeding practices. Nurses at the two institutions are organizationally separate and, thus, there are differences in nursing practices. Post-discharge data collection for all enrolled infants occurs in a high-risk infant follow-up clinic which provides comprehensive ongoing services to high-risk infants through an interdisciplinary team.

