### Sample

One hundred and twenty preterm infants (60/group) will be enrolled. Infants are included if they are less ≤ 32 weeks PMA at birth and parents provide informed written consent. Infants are excluded if they have known gastrointestinal, craniofacial, cardiovascular, neuromuscular, and/or genetic defects. Infants of both genders and all ethnic and racial backgrounds are recruited. We expect approximately 5 % of the sample to be Hispanic and 50 % to be Black/African American. Approximately 10 % of the sample is expected to be multiple gestation (twin or triplet). Two to three infants are enrolled per month; this number is based on data from the clinical setting, our experiences in previous studies, the length of the intervention, and our data collection processes. Infants who are medically unable to transition to oral feeding by 40 weeks PMA are excluded from further study.

Infants are recruited by research nurses who are experienced in neonatal care and trained in study procedures. Initial contact is generally made within 24 to 48 hours after the infant’s birth. A study brochure is provided to parents and a demonstration of study procedures using a doll is given. Parents are encouraged to think about participation for as long as they need; study nurses usually contact parents within 1 to 2 days of first contact to obtain parents’ decision.

A randomization scheme was created by the study statistician for study group assignment using Statistical Analysis Software (SAS 9.3, SAS Institute Inc., Cary, NC, USA). The random group assignments are placed on a card and sealed, only to be used after an infant was enrolled. Once enrolled, infants are randomly assigned to either the intervention or the control group by drawing a card from the assignment set. Parents of twins are allowed to request a single randomization card for both twins or to allow their infants to be randomized independently. Only one twin from a twinset where both infants were randomized with the same card will be included in the analysis.

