#### Power analysis

The proposed sample size for the study is based on associations between measures of feeding experience and components of neurobehavioral development and neurobehavioral organization discovered in our previous studies [18–21]. We anticipate 20 % attrition, primarily for medical conditions that arise or are diagnosed after enrollment. The sample size was determined by assuming each aim will be tested using 2-sided tests at *P* = 0.05. For the primary aim, we expect to detect an effect size of at least 0.7 standard deviation (SD) between groups on the final neurobehavioral score, with at least 90 % power using a 2-group *t*-test. However, a random effects model that takes into account the repeated measurements over time is proposed for the analyses of neurobehavior. Differences of the same effect size should improve the power to at least 95 % because of the additional number of observations. Although we have powered the study to test the primary aim, we also considered power for the additional aims. For secondary aim 1 involving a test of the effect of the intervention on cognitive function at 6 months, the same sample size analysis indicates a 2-unit difference (SD = 3) on cognitive development will be detected with 89 % power with only a 2-group *t*-test; the analysis of covariance (ANCOVA) should have more power. For secondary aim 2, the analyses and the sample size calculations are the same as with the primary aim. Secondary aim 3 will be tested in a manner similar to secondary aim 1 and so the sample size calculations should be similar. For the exploratory aim a sample of 96 infants in a test for zero correlation will provide at least 90 % power to detect *r* ≥ 0.26 and at least 80 % power to detect *r* ≥ 0.21.

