#### Neurobehavioral organization

The NAPI is used to measure neurobehavioral organization. The NAPI measures seven domains of neurobehavior and assesses the effect of NICU interventions. It is a non-intrusive, objective assessment of the infant’s maturity of functioning with construct validity with neonatal morbidity. We will use mean scores for each domain in our analyses with particular attention to the alertness and orientation score. The NAPI can be administered with the infant in an incubator or open crib and can be used if the infant is receiving oxygen; some items are not used if the infant is on mechanical ventilation. The assessment is done at least 30 minutes before feeding and uses a standardized format maximizing the opportunity to test various functions in appropriate behavior states. Most of the exam is observational and does not require handling the infant. The NAPI is administered at baseline, transition to oral feeding and NICU discharge assessments at the infant’s bedside by an experienced NAPI examiner. The NAPI assessment at 2 months corrected age is completed by the same examiners at the follow-up clinic. The NAPI is predictive of early developmental delay and later motor development, neurobehavior, and cognition; NAPI scores on alertness and orientation skills at 36 weeks PMA predict BSID III outcomes.

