#### Randomization to groups

A random assignment scheme was developed by the study statistician using a random number generator. Infants are assigned to groups at enrollment in equal numbers using 120 cards marked with one or other group contained in sealed envelopes and kept in a locked cabinet in the study office. Assignment to group is not blinded to parents, NICU staff, or the study nurses. The examiner for the major study outcomes is blinded to group assignment.

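### No described model includes NICU, and the baseline NAPI is collected but given no role in any described analysis; this costs precision, not validity

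*Protocol article*

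**What the plan says.** All places are in the protocol article.

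- **Setting.** One physician group staffs both NICUs, which is said to make feeding-related medical care similar. The next point is the contrast: "Nurses at the two institutions are organizationally separate and, thus, there are differences in nursing practices".
- **Randomization to groups.** "Infants are assigned to groups at enrollment in equal numbers using 120 cards", kept in sealed envelopes. No division of the cards by unit is described here or under Sample.
- **Neurobehavioral organization.** "The NAPI is administered at baseline, transition to oral feeding and NICU discharge assessments", and again at 2 months corrected age. Some items are skipped in ventilated infants.
- **Data management and analysis, primary aim.** The groups are compared on the NAPI by repeated-measures ANCOVA, fitted as a mixed model over transition to oral feeding, discharge and 2 months corrected age. No covariate is named.
- **Data management and analysis, secondary aims.** Aim 1 adjusts for the Neonatal Medical Index (NMI) and birth gestation. Aim 2 uses a "repeated-measures mixed-model approach with covariates (birth gestation, morbidity" in brackets. Aim 3 uses the same two covariates.
- **Intervention.** The recorded dose of attended feedings is also to be a covariate.

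**The concern.** The treatment contrast depends partly on what nurses do. Unit nursing staff may add attended gavage feedings in the intervention arm, and usual care is defined largely by how nurses handle, or do not handle, infants during gavage. Several secondary outcomes (feeding performance, time to full oral feeding, length of stay) are measured inside the unit. The plan itself names the unit as a source of differing practice, yet no described model accounts for it.

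The baseline value of the primary outcome is usually the first covariate to consider in an ANCOVA. Here it is measured and then not mentioned again.

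What is at stake is the width of the confidence intervals. Variation that could be explained stays in the error term, and a chance imbalance of arms across units goes uncorrected. It also matters that the covariate set be fixed in advance, because parents, NICU staff and study nurses all know the allocation.

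**Working it through.** **Inputs from the article**

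- Size: "One hundred and twenty preterm infants (60/group) will be enrolled" (Sample).
- Attrition: "We anticipate 20 % attrition, primarily for medical conditions that arise or are diagnosed after enrollment" (Power analysis). 120 × (1 − 0.20) = 96 evaluable, 48 per group.
- Test: "The sample size was determined by assuming each aim will be tested using 2-sided tests" at 0.05 (Power analysis).
- Primary effect: "we expect to detect an effect size of at least 0.7 standard deviation (SD) between groups on the final neurobehavioral score" (Power analysis), with power of at least 90%.
- Secondary aim 1: 2 units with SD 3, that is 0.667 SD, with 89% power.

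**Inputs not in the article (assumed)**

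- r, the correlation of baseline NAPI with the later score.
- R², the share of outcome variance explained by NICU.
- The split of infants between the two units.

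**Step 1. Reproduce the stated power.** Two-sample t-test, noncentrality = d × √(n/2), 94 degrees of freedom.

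- Primary: 0.7 × √24 = 3.43, power 92.4%. This agrees with at least 90%.
- Secondary aim 1: 0.667 × √24 = 3.27, power 89.8%. This agrees with 89% to within a point.
- Mean of three visits at 0.7 SD, variance factor (1 + 2ρ)/3: power 99.6%, 98.6%, 96.7% and 95.4% for within-infant correlation ρ = 0.3, 0.5, 0.7 and 0.8. This agrees with the stated 95% for the repeated-measures model.

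The sample size therefore rests on neither NICU nor baseline NAPI.

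**Step 2. What a unit difference would amount to.** For a difference of δ SD and a fraction p of infants in one unit, the variance share is δ²p(1 − p) / (1 + δ²p(1 − p)).

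| δ | share at p = 0.5 |
|---|---|
| 0.3 | 2.2% |
| 0.5 | 5.9% |
| 0.8 | 13.8% |

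An uneven split lowers these. At δ = 0.5 and p = 0.25, 0.25 × 0.1875 = 0.0469, and 0.0469/1.0469 = 4.5%.

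**Step 3. Chance imbalance.** With 48 per arm, an even split and no stratification, the SD of the arm difference in unit share is √(0.25 × 2/48) = 0.10. An imbalance of 20 percentage points (two SDs) with δ = 0.5 shifts the estimate by 0.20 × 0.5 = 0.10 SD, one-seventh of the 0.7 SD target. The unadjusted standard error already allows for such shifts; adjustment would remove them.

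**Step 4. Power after adjustment.** Single final score, 0.7 SD, 48 per group. Residual variance v = 1 − r² − R² (contributions assumed additive), noncentrality 3.43/√v, one degree of freedom lost per covariate.

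| Covariates | v | Power | Standard error smaller by | Worth, in unadjusted infants (96/v) |
|---|---|---|---|---|
| none | 1.00 | 92.4% | – | 96 |
| NICU, R² = 0.02 | 0.98 | 92.9% | 1% | 98 |
| NICU, R² = 0.05 | 0.95 | 93.6% | 3% | 101 |
| baseline, r = 0.2 | 0.96 | 93.4% | 2% | 100 |
| baseline, r = 0.3 | 0.91 | 94.5% | 5% | 105 |
| baseline, r = 0.5 | 0.75 | 97.5% | 13% | 128 |
| both, r = 0.2, R² = 0.02 | 0.94 | 93.8% | 3% | 102 |
| both, r = 0.3, R² = 0.05 | 0.86 | 95.5% | 7% | 112 |
| both, r = 0.5, R² = 0.05 | 0.70 | 98.2% | 16% | 137 |

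These r values are marginal correlations. If gestation and NMI are already in the model, only the partial correlation counts, and it may be smaller. In the three-visit model, power is already 95% or more (step 1), so there the gain would appear mainly as narrower intervals.

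**The case against.** The strongest reply is that this is an efficiency preference in a trial whose power already holds. Much of that reply stands.

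- **Bias.** A reader might infer that leaving NICU out biases the comparison. It does not: infants are randomized individually, and chance imbalance across units is part of the error that the standard error covers.
- **Exclusion of baseline NAPI.** A reader might infer that the primary model rules it out. The text does not show that. It names no covariates, and calling the model an ANCOVA implies at least one. The two-covariate lists belong to the secondary aims. A full protocol or SAP could name baseline NAPI. What can be said is that the article gives it no role.
- **Unstratified allocation.** A reader might infer that the cards were not divided by unit. The article is silent. If they were divided, step 3 largely falls away, but NICU would then belong in the model so that the analysis matches the design.
- **Mitigation.** Study nurses give at least half of the attended gavage feedings each day, fidelity is checked quarterly, tactile exposure in controls is recorded, one physician group covers both units, and follow-up takes place in one clinic setting. These may make the unit effect small. Dose as a covariate does not replace NICU: it is recorded after randomization and differs between arms by design.
- **Weak baseline.** An assessment of very immature infants, with items skipped under ventilation, may predict later scores poorly.

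The reply does not explain why a stated source of practice variation is missing from covariate lists that the article does spell out for the secondary aims, or why a baseline measure is taken with no stated use.

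**Conclusion.** The point holds as a loss of precision. NICU is absent from every described model, including the explicit covariate lists for the secondary aims, and the baseline NAPI has no role in any described analysis. The randomized comparison remains valid and the stated power figures stand.

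The size cannot be derived from the documents. Weak covariates (r up to 0.2, R² up to 0.02) add under 1 point each to a power of 92.4%, and about 1.4 points together. Moderate ones (r = 0.3, R² = 0.05) add about 3 points, and stronger ones (r = 0.5, R² = 0.05) nearly 6. These figures assume a single final score, additive contributions and no overlap with gestation or NMI; overlap would reduce them. Because the cost is so low, the change is worth making even if the gain proves to be at the small end.

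**What to change.** 1. Add NICU as a fixed effect to the primary mixed model and to every secondary ANCOVA or mixed model.
2. Name the primary covariates: birth gestation, NMI, NICU and, for each NAPI domain analysed, the baseline score on that domain.
3. Make baseline adjustment conditional on timing. The article does not say when the baseline NAPI is taken relative to allocation or to the first attended gavage. It should be used as a covariate only if it is measured before allocation or before the first attended gavage, and the plan should say which applies.
4. Where baseline items are missing because of ventilation, fill in the mean pooled over both arms and add a missing-value indicator, so that no randomized infant is dropped.

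The cost is one to three degrees of freedom per model (NICU, baseline NAPI, missing indicator) and a few lines of analysis text. No new data are needed. The trial was still recruiting at publication, so the change can be made before the outcomes are analysed.
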